## Introduction

### Background

Methadone is one of the most essential tools available to reduce opioid overdose deaths because it is safe, effective, and patient-preferred for the treatment of opioid use disorder (OUD) [1-3]. Access to methadone, one of 2 safe and effective OUD treatments, can reduce overdose mortality by up to 60% [4,5]. However, the promise of methadone is significantly diminished by geographic maldistribution of clinics and variations in the delivery of methadone maintenance treatment (MMT) across the country [6-8]. Treatment variations likely produce the observed wide-ranging MMT retention rates (30%-84%) [9,10].

MMT in the United States is delivered only by opioid treatment programs (OTPs; “methadone clinics”) certified and accredited by the federal government [11]. Variation in treatment quality and access maldistribution means that the impact of poor MMT outcomes is felt most acutely in rural communities as well as among populations who are Black, Hispanic, or Indigenous [12]. Unlike other health care environments, OTPs serve a daily average of more than 100 people in a narrow time window [13] and have been described as feeling “like bus stations” [14] rather than medical clinics. OTPs have been criticized as being unresponsive to patient need for treatment flexibility [15] and are not equipped to address what we know to be higher rates of patient trauma exposure and posttraumatic stress symptoms (PTSS) compared to the general population [16,17]. While MMT outcomes can be impeded by patient trauma [18], it is also possible that poor MMT outcomes and patient trauma are exacerbated by OTP practice and culture [19,20]. Patients report disenfranchisement from treatment decision-making through language referring to dosing as “privileges,” staff behavior described as “carceral” [21], and being tied to the OTP by “liquid handcuffs” due to daily required in-clinic supervised dosing [22].

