### Phase 2, Years 3-6: Hybrid, Cluster Randomized Controlled Trial

#### Overview

Aim 4: Quantify the effects of MPACT on methadone treatment practice change and clinic culture.Aim 5: Determine the efficacy of MPACT on methadone treatment retention and patient and staff PTSS outcomes.Aim 6: Evaluate the effect of patient and staff trauma on primary outcomes and staff MPACT implementation.

Findings from the pilot study will determine the preliminary effect size to confirm power analyses and final sampling for a hybrid type 1, 20-month cluster randomized controlled trial among 30 clinics, 600 patients (20 per clinic), and 480 staff (18 per clinic). This hybrid type 1 trial will focus primarily on MPACT’s effect outcomes while examining the association of MPACT implementation fidelity and acceptability and identifying the multilevel factors influencing implementation.

For the trial, the clinic is the unit of randomization. The intervention condition will be the MPACT intervention, and the control condition will involve accredited training about methadone that does not overlap aspects of the MPACT intervention. As shown in Table 2, we will allow a 20-month study period to accommodate staggered trial initiation through month 12 of year 2. Given the 20-month trial period, we will allow for new staff members to enroll through the end of the 7th month of their site’s trial period.

**Table 2 table2:** Cluster randomized controlled trial of Methadone Patient Access to Collaborative Treatment.

	Year 1			Year 2			Year 3			Year 4	
	Half 1	Half 2	Half 1		Half 2	Half 1		Half 2	Half 1		Half 2
Intervention arm clinics (n=15)	Start-up	Intervention	Intervention		Intervention	Intervention		Intervention	Intervention		Closeout
Control arm clinics (n=15)	Start-up	Usual care	Usual care		Usual care	Usual care		Usual care	Usual care		Closeout
Key processes	Randomization process finalized	Trial allows for staggered starts based on recruitment	Trial allows for staggered starts based on recruitment		Trial allows for staggered starts based on recruitment	Trial follow-up		Trial follow-up	Trial follow-up		Trial outcome analyses and dissemination

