### Statistical Analysis

Our primary outcome is patient time to first treatment interruption (confirmed in the pilot). Secondary outcomes include treatment retention (yes or no) at selected time points (1, 3, 6, and 12 months) and time to treatment discontinuation. To accommodate the clustering induced by nesting patients within clinics, we will use a mixed effects Cox proportional hazards model (shared frailty model) [61,62] to accommodate differential survival probability among clusters. The mixed model will include a random intercept for the clinic and a fixed treatment effect for MPACT or control assignment. We will also include patient-level covariates for age, sex, and time in MMT.

Our initial sample size calculation uses asymptotic normal results for log hazard ratio as well as sample size inflation factors (eg, Donner) [62] for cluster randomized trials. In designing the future R33 trial, we will make use of specific sample size methods for cluster randomized trials with time-to-event outcomes [63,64]. The relative frequency of first treatment interruption [65] is estimated as 66% at 12 months of MMT until we have confirmation from the pilot. We evaluate the number of clinics and number of patients, assuming that MPACT intervention reduces this frequency to 45% (n=240), 50% (n=300), and 55% (n=330). The power curves based on independent observations (no cluster effect) are shown in Figure 3. The graph shows that the recruitment of 30 clinics, with 20 patients per clinic, provides greater than 80% power to detect a difference in treatment interruption rates of 66% (control) and 55% (MPACT) with α=.05. Consistent with the cluster randomization trial design, we also consider the average number of patients per clinic as 10, 20, and 40 and different degrees of intraclinic clustering using intraclass correlation coefficients of 0.05 and 0.10.

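### The power above 80% stated for 66% versus 55% with 30 clinics of 20 patients assumes no clinic clustering; at the two ICCs the plan names it is about 50-54% and 36-39%

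*Protocol article*

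**What the plan says.** The Phase 2 Overview makes the clinic the unit of randomisation, with 15 clinics per arm, in a "cluster randomized controlled trial among 30 clinics, 600 patients (20 per clinic" per clinic). The Statistical Analysis section bases the initial sizing on normal theory for the log hazard ratio plus inflation factors for cluster trials. The control rate of first interruption "is estimated as 66% at 12 months of MMT until we have confirmation from the pilot". Three intervention rates are evaluated, "assuming that MPACT intervention reduces this frequency to 45% (n=240), 50% (n=300), and 55% (n=330"), and n is not defined.

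The section then states: "The power curves based on independent observations (no cluster effect) are shown in Figure 3". The next sentence reads: "The graph shows that the recruitment of 30 clinics, with 20 patients per clinic, provides greater than 80% power to detect a difference" in interruption rates of "66% (control) and 55% (MPACT) with α=.05". It adds that 10, 20 and 40 patients per clinic and ICCs of 0.05 and 0.10 are considered as well, but gives no power or number of clinics for them in the text.

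**The concern.** Patients in one clinic share staff, rules and culture, and the intervention acts on staff, so outcomes within a clinic are expected to be correlated. The planned Cox model has a clinic random intercept for that reason. A power figure for independent patients therefore does not describe a trial of 30 randomised clinics. The inflation factor named at the start of the calculation does not reach the one power figure the text reports.

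That sentence is the text's only power statement for 600 patients on the primary outcome. If an 11-point reduction is real and the ICC is near either value named, the trial would miss it about half the time or more. A reader relying on the stated power could take a null result as evidence of no effect.

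**Working it through.** **Inputs.** From the Statistical Analysis section: control rate 66% at 12 months; intervention rates 55%, 50% and 45%; alpha 0.05; ICCs 0.05 and 0.10. From the Phase 2 Overview and Table 2: 30 clinics of 20 patients, 15 clinics per arm. Assumed: two-sided test, equal cluster sizes, no dropout, proportional hazards.

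**Reproducing the stated figure (ICC 0, 66% vs 55%).**
- HR = ln(1-0.55)/ln(1-0.66) = 0.740, so |log HR| = 0.301.
- Expected events = 600 x (0.66+0.55)/2 = 600 x 0.605 = 363.
- Log-HR power = Phi(|log HR| x sqrt(events)/2 - 1.96) = Phi(2.866 - 1.96) = 81.8%.
- Two proportions, 300 per arm: Phi[(0.11 x sqrt(300) - 1.96 x sqrt(2 x 0.605 x 0.395)) / sqrt(0.66 x 0.34 + 0.55 x 0.45)] = Phi(0.801) = 78.8%.

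The stated power is therefore right for the log-HR method without clustering.

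**Adding clustering.** The design effect is DE = 1 + (20-1) x ICC. Events, or patients per arm, are divided by DE.

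| ICC | DE | Effective N | Effective events | Power, log HR | Power, two proportions |
|---|---|---|---|---|---|
| 0 | 1.00 | 600 | 363 | 81.8% | 78.8% |
| 0.01 | 1.19 | 504 | 305 | 74.8% | 71.6% |
| 0.02 | 1.38 | 435 | 263 | 68.4% | 65.1% |
| 0.05 | 1.95 | 308 | 186 | 53.7% | 50.5% |
| 0.10 | 2.90 | 207 | 125 | 39.1% | 36.5% |

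**Room for clustering in 600.** Events for 80% power = 4 x (1.96+0.8416)^2 / 0.301^2 = 347, so N = 347/0.605 = 573.6. The largest tolerable design effect is 600/573.6 = 1.046, which gives ICC = 0.046/19 = 0.0024. By two proportions the unclustered requirement is already 618.

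**Sensitivity for 66% vs 55% (ICC 0.05, then 0.10).**
- One-sided alpha: 63-66%, 49-52%.
- t reference with 28 degrees of freedom: 51%, 37%.
- Events over all 20 months, assuming exponential times: 65%, 48%.

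None reaches 80%.

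**The larger effects, 600 patients (two proportions to log HR).**
- 66% vs 50%: 81-84% at ICC 0.05; 65-68% at ICC 0.10.
- 66% vs 47%: 79-82% at ICC 0.10.
- 66% vs 45%: 96-97% at ICC 0.05; about 86-89% at ICC 0.10.

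**The bracketed n.**

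| Intervention rate | Stated n | Total for 80% power, no clustering | That rate x 600 |
|---|---|---|---|
| 45% | 240 | 162-174 | 270 |
| 50% | 300 | 277-298 | 300 |
| 55% | 330 | 573-618 | 330 |

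The values 300 and 330 match the last column exactly, and 300 is also close to the two-proportion total of 298. The value 240 matches neither column. It is near one clustered requirement (10 per clinic, ICC 0.05: 238 patients, so 24 clinics), but the same setting needs 403 for 50% and 832 for 55%, so it cannot be the common definition.

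**The case against.** The strongest reply is that the section hides nothing. It labels the curves as having no cluster effect, calls the calculation initial, names inflation factors and commits to sample-size methods for cluster trials with time-to-event outcomes. The Overview and Discussion say that the pilot will inform power and final sampling. The caption of Figure 3 concerns clinics and patients for 80% power and defines ICC, so the figure may carry cluster-adjusted curves. All of this stands, and it rules out saying that the authors overlooked clustering or never worked through the ICCs. It does not correct the printed sentence, which gives an unclustered power to a named number of clinics. A single-arm pilot in two clinics can also say little about an ICC.

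The shortfall concerns 66% versus 55%. A reader might infer that the trial is underpowered for every effect considered. It is not: 50% keeps 80% power at ICC 0.05, and 45% keeps it at both ICCs. Nor has the plan adopted a single ICC; 0.05 and 0.10 are values it considers.

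A reader might also infer a likely ICC from the 30-84% spread of retention rates in the Background. The documents do not support this. Those rates come from cited sources, are not described as between-clinic variation, and concern retention rather than first missed dose.

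**Conclusion.** The statement is wrong for the design as described. For 66% versus 55% with 600 patients in 30 clinics, power is about 82% (log HR) or 79% (two proportions) only at ICC 0. It is about 50-54% at ICC 0.05 and 36-39% at ICC 0.10. These figures rest on a two-sided 0.05 test, equal clusters of 20, no dropout and the standard design effect, which is an approximation for a time-to-event outcome. The sensitivity results show that none of these choices of test or follow-up restores 80% at either ICC.

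The bracketed n is a secondary labelling point. A reader might conclude that all three values are wrong, or that 330 contradicts the 600 patients. Neither follows, because n is undefined and 300 and 330 equal 50% and 55% of 600. What holds is that n needs a definition and that 240 fits neither an unclustered required total nor 45% of 600.

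**What to change.** Replace the power sentence with cluster-adjusted figures and name the method and sidedness. For example: with a two-sided 0.05 test and design effect 1 + 19 x ICC (range: two proportions to log hazard ratio), 30 clinics of 20 patients give about 81-84% power for 66% versus 50% at ICC 0.05, and about 86-89% for 66% versus 45% at ICC 0.10 (about 79-82% for 66% versus 47%); power for 66% versus 55% is about 50-54% and 36-39% respectively. If Figure 3 holds ICC curves, cite the power from those curves. Define the bracketed n as a total, a per-arm number or a count of events, and correct n=240 to match.

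The cost is rewording, possibly a relabelled figure, and a less favourable stated power. No extra patients are needed for the correction. Keeping 66% versus 55% as the target at 80% power would be a separate design decision: at 20 patients per clinic it needs about 56-61 clinics at ICC 0.05 or 84-90 at ICC 0.10.

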**Figure 3 figure3:**
[figure not shown]
Number of clinics and patients for 80% power (vs 66% treatment interruption rate), MPACT trial. ICC: intraclass correlation coefficient; MPACT: Methadone Patient Access to Collaborative Treatment.

## Results

The pilot study is funded by the National Institute on Drug Abuse (award R61DA059889, funded September 2023), and the field trial will be funded under the associated R33 mechanism in September 2025. The pilot study was completed on March 17, 2025. We are currently analyzing the pilot study findings. The randomized controlled trial will begin in December 2025.

## Discussion

The MPACT study will provide a foundation for an evidence-based, staff-level intervention aimed at improving patient retention in MMT. We anticipate a decrease in reported levels of VT and PTSS among staff and an increase in methadone treatment retention among patients. The pilot outcomes are focused primarily on implementation with a preliminary indication of impact or effectiveness. The preliminary outcomes from the pilot will inform the final sampling to properly power the study. The trial outcomes are focused both on the implementation and effectiveness of the MPACT intervention. Future studies should examine the individual components of MPACT to determine their differential contributions to the primary outcome of patient MMT retention and to secondary outcomes of staff and patient reduction in stress symptoms.

## Appendix

Multimedia Appendix 1 Peer review report from ZDA1 SKP-E (O2) - National Institute on Drug Abuse Special Emphasis Panel HEAL Initiative: Translating Research to Practice to end the Overdose Crisis (National Institutes of Health, USA).

## Abbreviations

DSA: data sharing agreement
MMT: methadone maintenance treatment
MPACT: Methadone Patient Access to Collaborative Treatment
OTP: opioid treatment program
OUD: opioid use disorder
PCL-5: Posttraumatic Stress Disorder Checklist
PTSS: posttraumatic stress symptoms
RE-AIM: Reach, Effectiveness, Adoption, Implementation, and Maintenance
TICA: trauma-informed clinic self-assessment
VT: vicarious trauma
